#### Primary outcome

The primary outcome of this study is to statistically analyze the recurrence rate 1 year after FESS and its correlation with traditional Chinese medicine syndrome types and eosinophil infiltration, in order to establish a predictive model for CRSwNP recurrence.

The definition of recurrence is that mucosal lesions (nasal polyps, mucus purulent discharge, and/or mucosal inflammation and edema) are seen under nasal endoscopy, the symptoms persist for 1 month without any alleviation, and maximum drug treatment is required [22].

#### Secondary outcomes

Scores and efficacy assessments will be used as secondary outcome indicators in this trial, to judge whether timely drug treatment and necessary secondary surgical intervention will be needed.

The efficacy assessment criteria referred to the *European Position Paper on Rhinosinusitis and Nasal Polyps (EOPS)* 2020 [1] and the Chinese guidelines for diagnosis and treatment of chronic rhinosinusitis (2018) [2]: nasal congestion, runny nose, head and face pain, hyposmia, sleep disturbance, abnormal findings in nasal endoscopy, and drug maintenance treatment are still needed. The presence of any one of the above symptoms is considered as partial control of the disease, three or above conditions as conditions uncontrolled, and free from any one symptom as complete control of the disease.

### Safety assessments

The present study prospectively explored the correlation among postoperative recurrence of CRSwNP and TCM syndrome types and tissue inflammatory cell infiltration types, mainly collecting the data of patients for analysis, and cells of pathological sections will be calculated. There will no specially designed intervention in this study, and we will simply follow the real-world intervention.

### Sample size calculation

This study includes a sample size of 200 cases. The sample size was calculated according to the recurrence rate of different TCM syndrome groups.

There are 4 exposure factors of interest in this study. In the previous study [17], the expected relative risk of the 3 exposure factors was obtained from 71 patients, and then the sample size was calculated according to each of the 3 exposure factor groups, and then the maximum of these was taken as the final sample size.

Preliminary research on four types of traditional Chinese medicine syndromes shows that the recurrence rate (relative risk) of the syndrome of spleen qi deficiency group is Pmax = 11/26 = 42.3%, the recurrence rate (relative risk) of the syndrome of dampness and heat in the spleen and stomach group is 2/32 = 6.25%, and the recurrence rate (relative risk) of the syndrome of stagnated heat in the gallbladder group is Pmin = 0/13 = 0% [17]. According to the *α* = 0.05, *β* = 0.2, and with a sample ratio of 1:2 exposed to a certain TCM syndrome characteristic group and not exposed to a certain TCM syndrome characteristic group, the sample size of each exposure factor group was calculated using PASS 11 software, following the method of sample size calculations in clinical research. Considering that the dropout rate of the research subjects is 10%, we will select the group with the largest appeal sample size. That is, the minimum sample size required for each group is 20 in the exposed group and 40 in the nonexposed group. So, to complete the observation study of four exposure factor groups, the minimum total sample size is 80 cases. The total sample size of this study is 200 cases, which meets the research requirements. It should be noted that at least 20 patients exposed to each type of traditional Chinese medicine syndrome feature need to be included in the sample. At the same time, 200 cases met the sample size of unconditional logistic regression.

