### Statistical analysis

SPSS 23.0 software is used for data analysis.For quantitative data, *t*-test and nonparametric test are used to evaluate the pairwise difference between normally distributed data and non-normally distributed data, respectively. For qualitative data, chi-square test is applied for analysis. *P* < 0.05 is considered statistically significant.Apply logistic regression model to evaluate the relative risk of each variable and its correlation with nasal polyp recurrence.Different traditional Chinese medicine syndromes are entered into a regression model, and the predictive value is determined by the area under the ROC curve (AUC). AUC > 0.9: high predictive value of the model; 0.7 < AUC ≤ 0.9: moderate predictive value. When 0.5 < AUC ≤ 0.7, the optimal diagnostic cut-off point is obtained when the Youden index (sensitivity + specificity − 1) of predictive value is maximized.

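### The planning data contain a syndrome type with no recurrences (0/13); if that cell is empty again, the planned ordinary logistic model gives no usable odds ratio, Wald test or predicted risk for that type

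*Protocol article*

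**What the plan says.** The section on sample size calculation states that "the expected relative risk of the 3 exposure factors was obtained from 71 patients". It reports recurrence in three of the four types: spleen qi deficiency, "Pmax = 11/26 = 42.3"%; damp heat in the spleen and stomach, 2/32 = 6.25%; and, as the minimum, "the recurrence rate (relative risk) of the syndrome of stagnated heat in the gallbladder group is Pmin" = 0/13 = 0%. No rate is given for the lung qi type. The section requires at least 20 patients of each type within a total of 200, and says that 200 is enough for an unconditional logistic regression.

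The section on statistical analysis names SPSS 23.0 and a 0.05 significance level. For categorical data it says "For qualitative data, chi-square test is applied for analysis". For recurrence it says "Apply logistic regression model to evaluate the relative risk of each variable", with the syndrome types entered in the model and its predictive value judged by the area under the ROC curve. It names neither the test for a coefficient (Wald or likelihood ratio) nor the reference type. The primary outcome section makes the link between recurrence, syndrome type and eosinophil infiltration the basis of a prediction model.

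**The concern.** The method chosen for the primary objective has no finite estimate when applied to the plan's own planning data. When one category of a factor has no events, ordinary maximum likelihood pushes its coefficient towards minus infinity. The software stops at an arbitrary large value with a very large standard error.

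At stake is the contrast that the planning data suggest is the largest, gallbladder against spleen qi. The results table could show an odds ratio of essentially zero, an interval with no useful limits and a Wald p-value near 1. The prediction model would also give every gallbladder-type patient a risk of zero, which 0 out of a few dozen patients cannot justify. The gallbladder type is Cohort 1 in the article; if it served as the reference, all the syndrome odds ratios would be unusable.

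**Working it through.** **Inputs.** Pilot counts 11/26, 2/32 and 0/13 (total 26 + 32 + 13 = 71, with 13 recurrences), the minimum of 20 per type, the 10% dropout and the total of 200 all come from the sample size section. One assumption is added: scaling the pilot mix to 200 gives 200 × 13/71 = 37 gallbladder patients, 73 spleen qi and 90 damp heat. This leaves no room for the lung qi type, so 37 is on the generous side.

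**The plan's own figure.** "the minimum sample size required for each group is 20 in the exposed group and 40 in the nonexposed group" cannot be reproduced with certainty, because the recurrence rate in the nonexposed group is not given. With a two-sided 5% test, 80% power, a 1:2 ratio and 10% dropout, 6.25% against 42.3% gives 19 and 38. That is close, but other comparators give other sizes. The point below uses only the pilot counts and the minimum of 20.

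**1. Ordinary logistic model on the pilot counts** (spleen qi as reference, syndrome type only, stopped at 20 iterations).
- Gallbladder: b = −20.9, SE = 11,148, Wald p = 0.9985.
- Damp heat: b = −2.40, SE = 0.83, Wald p = 0.004. This contrast survives.
- Likelihood-ratio test of syndrome type: 17.2 on 2 df, p = 0.0002.
- With gallbladder as reference, both contrasts have SE of about 11,148 and Wald p above 0.998.

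A larger sample does not cure an empty cell: 0/37 against 31/73 gives SE = 6,608 and Wald p = 0.997. A single event does: with 1/37, b = −3.28, SE = 1.04 and p = 0.0016.

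**2. Firth penalised likelihood on the same counts.** With one categorical factor this equals adding one half to each cell: OR = (0.5/13.5) / (11.5/15.5) = 0.050. The profile-likelihood 95% interval is 0.0004 to 0.45, p = 0.0037. The fitted gallbladder risk is 0.5/14 = 3.6%, not 0.

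**3. How probable is an empty cell?** For a fixed true risk p it is (1 − p)^n.

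| True risk | n = 20 | n = 37 |
|---|---|---|
| 2% | 67% | 47% |
| 5% | 36% | 15% |
| 10% | 12% | 2% |

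The pilot does not pin down p: the exact two-sided 95% upper limit for 0/13 is 1 − 0.025^(1/13) = 24.7%. Averaging over what 0/13 leaves open gives the predictive probability. With a uniform prior it is 14/(14 + n), and with a Jeffreys prior it is B(0.5, 13.5 + n)/B(0.5, 13.5).

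| n | Uniform | Jeffreys |
|---|---|---|
| 18 (20 less 10% dropout) | 44% | 65% |
| 20 | 41% | 63% |
| 37 | 27% | 51% |
| 50 | 22% | 46% |

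**4. Chi-square test of the same contrast.**
- Pilot, 0/13 against 11/26: chi-square 7.66, p = 0.0056 (Yates 0.017, Fisher 0.0067).
- 0/20 against 8/20: p = 0.0016 (Yates 0.0057, Fisher 0.0033).
- 0/37 against 31/73: p = 3 × 10⁻⁶.

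The smallest expected counts are 13 × 11/39 = 3.7 in the pilot and 20 × 8/40 = 4.0 at 20 per group. At the overall pilot rate, a type of 20 expects 20 × 13/71 = 3.7 recurrences and a type of 37 expects 6.8.

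**The case against.** A reader might infer that the chi-square test fails too, so that the plan would miss its largest contrast altogether. The documents do not support this. Chi-square needs no finite odds ratio, and it finds that contrast significant in the pilot and at each size checked. Small expected counts matter only near the 20-patient minimum and for weaker contrasts: gallbladder against the rest, 0/20 against 9/40, gives p = 0.021 uncorrected but 0.055 with Yates.

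A reader might also infer that separation is likely and would wreck the whole model. The first part goes further than 0/13 allows: the probability is well below one half at moderate true risks, and one recurrence restores a finite fit. The second holds only if the empty type is the reference. One empty category is quasi-complete separation, and with another reference the remaining contrasts are still estimable.

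Further objections carry some weight. The p-value near 1 belongs to the Wald test; the likelihood-ratio test stays significant, and the article names neither. The ROC area and the Youden cut-off can still be computed. The check fits syndrome type alone, whereas the plan also involves eosinophil infiltration; however, adding a covariate cannot remove the separation caused by a type without events.

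The strongest objection is that a fallback for sparse data usually sits in a statistical analysis plan, which is not shown. That would settle the matter if the article were silent on method. It is not: it commits to unconditional logistic regression and prints the planning count on which that method has no estimate.

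**Conclusion.** The point holds in a conditional form. If the gallbladder type again has no recurrences, the planned maximum-likelihood odds ratio for that type is not finite, its Wald p-value says nothing and its predicted risk is 0. All syndrome contrasts share the problem if that type is the reference. The risk is substantial rather than certain: roughly 41% to 63% with 20 patients of that type and 27% to 51% with 37. These figures assume that the pilot patients resemble the cohort, and they depend on the prior; 37 further assumes the pilot's mix of types. The chi-square analysis needs only a small-count safeguard. The change is worth making before the data are analysed, because a switch of method after an infinite odds ratio has been seen would be post hoc.

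**What to change.** In the statistical analysis section, state that the recurrence model will be fitted by Firth's penalised likelihood, with profile-likelihood confidence intervals and tests in place of Wald ones. Name in advance a reference type that is expected to be well populated and to have recurrences; damp heat, the largest pilot group with 2/32, is one candidate.

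As a secondary change, specify Fisher's exact test, or the Fisher-Freeman-Halton test for larger tables, whenever an expected count is below 5.

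The cost is a few lines of text, R or an SPSS extension for the Firth fit, and slight shrinkage of the estimates. The sample size and data collection do not change.

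### The stated minimum of 20 exposed and 40 non-exposed is not the largest of the three pilot calculations; the damp-heat contrast needs about 40 and 80, although the planned total of 200 can still be adequate

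*Protocol article*

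**What the plan says.** All of this is in the protocol article, Sample size calculation, unless noted.

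- Planning inputs: "the expected relative risk of the 3 exposure factors was obtained from 71 patients". The recurrence rates are given as "the syndrome of spleen qi deficiency group is Pmax = 11/26 = 42.3"%, "the syndrome of dampness and heat in the spleen and stomach group is 2/32 = 6.25"%, and 0/13 = 0% for stagnant heat in the gallbladder.
- Design parameters: alpha 0.05, beta 0.2, and a 1:2 ratio of patients with a given syndrome to patients without it, computed in PASS 11.
- Selection rule: one calculation per exposure group, then, with 10% dropout considered, "we will select the group with the largest appeal sample size".
- Result: "That is, the minimum sample size required for each group is 20 in the exposed group and 40 in the nonexposed group". From this the article derives a minimum total of 80 for four groups and judges 200 sufficient.
- Floor: "at least 20 patients exposed to each type of traditional Chinese medicine syndrome feature need to be included in the sample".
- The paragraph refers to preliminary research on four syndrome types, but prints three rates and speaks of three exposure factors.

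The Statistical analysis section names the chi-square test for qualitative data. Outcome measurements restricts analysis to patients who complete the one-year follow-up.

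**The concern.** The rule is to take the largest requirement. The three pilot groups add up to the whole pilot (26 + 32 + 13 = 71), so a non-exposed rate for each contrast can be formed from the other two groups. The spleen-qi contrast is very wide and needs few patients. The damp-heat contrast is much narrower and should drive the maximum, yet the stated 20/40 is close to what spleen-qi alone needs.

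The 20 is carried forward as the floor for every syndrome and as the basis of the minimum total of 80. A reader would take a cohort that just meets the floor to have 80% power. Recurrence by syndrome type is part of the primary outcome, so the power attached to that floor matters. The fourth cohort, lung-qi, receives the same floor without any planning rate in this calculation.

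**Working it through.** **Inputs.** Exposed rates are as printed. Non-exposed rates are my assumption: the other two pilot groups pooled.

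| Contrast | Exposed p1 | Non-exposed p2 |
|---|---|---|
| Spleen-qi | 11/26 = 0.4231 | (2+0)/(32+13) = 2/45 = 0.0444 |
| Gallbladder | 0/13 = 0 | (11+2)/(26+32) = 13/58 = 0.2241 |
| Damp-heat | 2/32 = 0.0625 | (11+0)/(26+13) = 11/39 = 0.2821 |

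Two-sided alpha 0.05 (sidedness is not stated), power 0.80, k = 2 non-exposed per exposed.

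**Formula (pooled two-proportion).** With p̄ = (p1 + 2·p2)/3,

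n_exposed = [1.960·√(1.5·p̄(1−p̄)) + 0.8416·√(p1(1−p1) + p2(1−p2)/2)]² / (p1 − p2)²

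For damp-heat, p̄ = 0.2089. The two terms are 0.9758 and 0.3365, and the difference is 0.2196. So n = (1.3123/0.2196)² = 35.7, rounded up to 36. Dropout: 36/0.9 = 40.

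| Contrast | n exposed | Rounded | After dropout (exposed/non-exposed) |
|---|---|---|---|
| Spleen-qi | 12.5 | 13 | 15/30 |
| Gallbladder | 24.3 | 25 | 28/56 |
| Damp-heat | 35.7 | 36 | 40/80 |

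**Attempt to reproduce 20/40.** The nearest two-sided result for spleen-qi is the continuity-corrected one: 17, or 19 after dropout (19/38). Under that method spleen-qi is the smallest of the three; gallbladder needs 35 and damp-heat 48. A pairwise comparison of spleen-qi with damp-heat also lands near 20 (19 unpooled, 22 continuity-corrected, after dropout), but it is not the exposed versus non-exposed contrast described.

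**Sensitivity to the unstated test and sidedness.** Damp-heat, exposed, after dropout:

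| | Pooled | Continuity-corrected | Unpooled | Arcsine |
|---|---|---|---|---|
| Two-sided | 40 | 48 | 30 | 36 |
| One-sided | 32 | 39 | 24 | 28 |

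The range is 24 to 48; no variant gives 20.

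**Exact power of the two-sided chi-square test without continuity correction**, by enumeration of both binomials:

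| Exposed/non-exposed analysed | Spleen-qi | Gallbladder | Damp-heat |
|---|---|---|---|
| 20/40 (stated minimum) | 95% | 82% | 54% |
| 18/36 (after 10% dropout) | 94% | 73% | 48% |
| 18/162 (floor of 20 within 200, after dropout) | 99% | 90% | 59% |
| 45/135 (even split of 180 completers) | >99% | >99% | 94% |

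At the pilot mix, damp-heat is 32/71 = 45% of patients, or about 81 of 180 completers against 99, and its power is 98%.

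**Floor needed for damp-heat within 200.** With 180 completers, 28 exposed against 152 others gives 80%. Enrolled: 28/0.9 = 31.1, so about 32.

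**Minimum total.** The plan's 80 is 4 × 20. The same logic with 40 per syndrome gives 4 × 40 = 160, still within 200.

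**The case against.** The strongest reply is that nothing about enrolment changes. The study enrols 200, so 20 damp-heat patients would face about 180 others, not 40. Damp-heat was also the commonest pilot type; its share would have to fall from 45% to 10% for the floor to bind. This stands. A reader might infer from the 54% that the trial is underpowered, and the documents do not support that: at an even split or the pilot mix, power for this contrast is well above 80%.

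Second, the comparator is derived, not printed, and it contains no lung-qi patients. The Background says that lung-qi has higher recurrence, which would raise the non-exposed rate and lower the requirement. This is fair as a limit. On the normal approximation, though, a non-exposed rate of about 38% (20/40 analysed) to 40% (18/36 analysed) would be needed for 80% power, against 28.2% in the pilot.

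Third, one might read the result as 20/40 failing every contrast except spleen-qi. That is too strong. Gallbladder exceeds 20 under the pooled formula, but its exact power is 82% at 20/40 and 90% at the floor within 200. It drops to 73% only with 36 non-exposed patients, which a cohort of 200 would not produce.

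Finally, a reader might conclude that the pilot covered only three types, or that lung-qi can hardly reach 20 patients because the pilot shows none. Neither can be settled here: how the pilot selected patients is not shown, and the Background cites prior work on lung-qi recurrence. Only the inconsistency can be flagged.

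**Conclusion.** The point holds for the stated minimum and for the floor, not for the total. Under the plan's own rule and pilot counts the largest contrast is damp-heat, at about 40/80 by the two-sided pooled method: twice the printed 20/40. A damp-heat cohort at the floor of 20 within the 200 has about 59% power, against the stated 80%; spleen-qi and gallbladder are adequate there.

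This rests on each non-exposed rate being the pooled rate of the other two pilot groups, on 10% dropout falling evenly, and, for the headline figure, on a two-sided test. The exact requirement moves with the test variant; that it exceeds 20 does not.

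For lung-qi the calculation contains no rate, so it supports no power statement for that cohort.

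**What to change.** 1. Re-run the three contrasts and print the comparator rate, sidedness and test for each.
2. Replace 20/40 with the true maximum (40/80 under the pooled method), and re-derive the minimum total on the plan's own four-group logic as 160 in place of 80.
3. Restate the damp-heat floor as about 28 completers (about 32 enrolled) within the 200, or keep 20 and state that it gives about 59% power for that contrast. The other syndromes need not inherit the damp-heat floor.
4. Reconcile the mention of four syndrome types with the three rates that account for all 71 pilot patients, and state that the 80% power claim does not extend to lung-qi.

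The cost is one re-run in PASS and one rewritten paragraph. The stated minimum becomes less favourable; the total stays at 200, with no extra patients.

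### 200 cases are said to suffice for logistic regression, but the protocol's own rates give about 33 to 41 recurrences: enough for syndrome type, marginal with eosinophils, too few for a joint model of the baseline variables

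*Protocol article*

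**What the plan says.** Under Sample size calculation, the protocol article sets the total ("This study includes a sample size of 200 cases"). It derives 20 exposed and 40 non-exposed patients per syndrome from a pilot study ("the expected relative risk of the 3 exposure factors was obtained from 71 patients"), allows 10% dropout, and then adds: "At the same time, 200 cases met the sample size of unconditional logistic regression". No calculation accompanies that last statement.

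The pilot recurrence counts are spleen qi deficiency "Pmax = 11/26 = 42.3"%, "the syndrome of dampness and heat in the spleen and stomach group is 2/32 = 6.25"%, and "the syndrome of stagnated heat in the gallbladder group is Pmin = 0/13 = 0"%. No figure is given for the fourth type, deficiency and cold in lung qi.

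The Primary outcome section relates one-year recurrence to syndrome type and eosinophil infiltration "in order to establish a predictive model for CRSwNP recurrence". Study settings and participants describes a multiple regression on the same two factors, and lists general information, medical history, symptom VAS, Lund-Kennedy and Lund-Mackay scores as baseline data. Outcome measurements limits the analysis to patients who keep to the one-year follow-up.

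Statistical analysis applies logistic regression to each variable, then enters the syndromes in a regression model of which "the predictive value is determined by the area under the ROC curve". An AUC above 0.7 and up to 0.9 is called moderate, and above 0.9 high.

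**The concern.** What a logistic model can support depends on the number of recurrences, not the number of patients. A two-proportion calculation for one syndrome against the rest says nothing about how many predictors a multivariable model can carry. The sentence therefore gives an assurance that nothing in the section establishes, and it sets no limit on the model.

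The predictive model is part of the primary outcome, and the Discussion looks ahead to targeted perioperative treatment guided by it. If many predictors are entered on few recurrences, the AUC computed in the same patients is too high. The fixed 0.7 and 0.9 cut-points could then label a model as useful when it would not predict recurrence in new patients.

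**Working it through.** **1. The plan's own figure.** The logistic statement has no inputs and cannot be reproduced. The one calculation with inputs can be approached: spleen qi against the rest, 11/26 = 42.3% against 2/45 = 4.4%, two-sided 5% level, 80% power, ratio 1:2, continuity-corrected, gives 17/34. Dividing by 0.9 for dropout gives 19/38, close to the stated 20/40. That is a comparison of two proportions and has no bearing on a model with several predictors.

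**2. Expected recurrences** = N × rate.
- Pilot rate: (11 + 2 + 0)/(26 + 32 + 13) = 13/71 = 18.3%.
- All enrolled: 200 × 13/71 = 36.6.
- Completers: 200 × 0.9 = 180, and 180 × 13/71 = 33.0.
- Assuming lung qi recurs like spleen qi and the four groups are equal: (42.3 + 42.3 + 6.25 + 0)/4 = 22.7%, so 180 × 0.227 = 40.9.

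**3. Parameters supported.** At 10 events per parameter (a common benchmark, assumed here and not in the protocol), 33.0/10 = 3.3, 36.6/10 = 3.7 and 40.9/10 = 4.1.

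**4. Events per parameter and false labels.** The last column is the share of simulated studies in which a maximum-likelihood model of pure noise reaches an apparent AUC above 0.7 (n = 180, recurrence rate 18.3%, a four-level factor plus independent normal covariates, 1,500 runs per row).

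| Model | Parameters | Events per parameter (33 events) | Noise AUC above 0.7 |
|---|---|---|---|
| Syndrome type | 3 | 11.0 | 0.2% |
| Syndrome + eosinophils | 4 | 8.3 | 1.0% |
| Joint model, assumed size | 10 | 3.3 | 22% |
| Joint model, assumed size | 15 | 2.2 | 59% |

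A repeat simulation gave 55% with 15 parameters. At the 22.7% rate, the figures for 10 and 15 parameters are 12% and 43%.

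**5. Cross-check by shrinkage.** The sample size for an expected shrinkage of 0.9 is n = p / [(0.9 − 1) × ln(1 − R²/0.9)]. With the pilot's Cox-Snell R² of 0.215, which is probably optimistic, n = 110, 147, 366 and 549 for 3, 4, 10 and 15 parameters. The two small models fit within 180 and the larger ones do not. With a weaker assumed R² (15% of its maximum of 0.614), 3 and 4 parameters would need 278 and 371, so even the small models depend on syndrome being a strong predictor.

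**6. A group without recurrences.** The pilot has 0/13 in the gallbladder group, and the plan accepts as few as 20 patients per syndrome. With no recurrences in a group, its ordinary logistic coefficient cannot be estimated. The chance is (1 − rate)^n. At an assumed true rate of 2% it is 0.98^20 = 67% with 20 patients and 40% with 45; at 6.25% it is 28% and 5%.

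**The case against.** The strongest defence is that the model whose AUC is labelled is small. Statistical analysis enters the syndromes, which take 3 parameters and have 11 events each; that passes the benchmark. Applying logistic regression to each variable may mean one variable at a time, and no section says that all baseline data enter one model. This stands. A reader might infer that 200 patients are too few for any logistic model here, or that the AUC labels would often reward noise. The documents support neither: for 3 or 4 parameters noise passes 0.7 in 1% of studies or fewer, and the high rates need about 10 or more parameters, a number the protocol neither states nor rules out.

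The recurrence count is also uncertain. The pilot omits lung qi, for which the Background reports higher recurrence, and at 41 events syndrome plus eosinophils just passes (40.9/4 = 10.2). The Background's 40% would give 72 events, but it is an 18-month figure; even so it supports only about 7 parameters.

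Nor is noise the planning scenario. The pilot counts give a syndrome-only AUC of (11 × 50.5 + 2 × 28)/(13 × 58) = 0.81, itself an apparent value, so a moderate label could well be earned.

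Finally, a predictor list and optimism correction may sit in an analysis plan that is not shown. Their absence from the article is not the point. The point is the affirmative adequacy statement, and cut-points that are fixed without saying which AUC they apply to.

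**Conclusion.** The adequacy statement is not supported by the protocol's own figures. About 33 to 41 recurrences among completers carry 3 to 4 parameters: syndrome type is feasible, syndrome plus eosinophils (the pair named in the primary outcome) is marginal at 8.3 events per parameter, and a joint model of the collected baseline variables is not supported at about 2 to 3. The AUC labels carry little optimism for the small models, but would call noise moderate in about 22% of studies with 10 parameters and 55 to 59% with 15.

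This rests on the pilot rate applying to the one-year endpoint, 10% dropout, the assumed benchmark of 10 events per parameter, and, for the larger models only, an assumed parameter count. It does not show that the planned syndrome model fails.

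**What to change.** - Replace the adequacy sentence with a statement that about 33 to 41 recurrences are expected, supporting 3 to 4 model parameters, and give the rates behind that range.
- Limit the primary model to syndrome type plus eosinophil infiltration (4 parameters). Pool syndrome types before adding any severity score: two pooled types plus eosinophils use 2 parameters and leave room for one or two scores.
- Use a penalised fit such as Firth's if a syndrome group has no recurrences. This is likely if the true gallbladder rate is near 2% and the group is near the minimum of 20.
- Apply the 0.7 and 0.9 bands to the bootstrap optimism-corrected AUC, reported with a 95% confidence interval.

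The cost is a change of wording, one bootstrap run and a slightly lower reported AUC. No further recruitment or data collection is required.
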